## Abstract

Introduction: Osteoporosis is a major public health concern among postmenopausal women, characterized by decreased bone mineral density and microarchitectural deterioration, which lead to fragility fractures, pain, functional impairment, sleep disturbances, and a reduced quality of life. Exercise, particularly strength, weight-bearing, and balance training, represents a key non-pharmacological approach to prevention and management. Pilates, a low-impact, core-centered method increasingly incorporated into rehabilitation settings, appears especially suitable for women with osteoporosis. However, high-quality randomized controlled trials concurrently evaluating its effects on pain, balance, sleep, autonomy, and health-related quality of life remain scarce. Objective: To examine the efficacy and feasibility of a Pilates-based exercise program in improving pain, balance, sleep quality, functional autonomy, and quality of life in postmenopausal women with osteoporosis. Methods: A single-blind, parallel-group, randomized controlled trial will be conducted over 12 weeks at Physiocare Madrid (Spain). A total of 126 (63 per group) postmenopausal women aged 50–80 years, diagnosed with osteoporosis by densitometry or with a prior fragility fracture, will be randomly assigned (1:1; OxMaR software, version 2014) to one of two groups: (a) Experimental group: supervised Pilates mat sessions, 60 min, twice weekly for 12 weeks; or (b) Control group: ergonomics education for activities of daily living, two 60 min sessions held six weeks apart. Outcome assessors will remain blinded to group allocation. Evaluations will be conducted at baseline and post-intervention. Outcome measures will include balance and mobility (Timed Up and Go Test; Functional Reach Test), functional autonomy (Functional Independence Measure), pain intensity (Visual Analog Scale), sleep quality (Pittsburgh Sleep Quality Index), health-related quality of life (WHOQOL-BREF; QUALEFFO-41), and treatment satisfaction (CSQ-8). Feasibility parameters (recruitment, adherence, retention, and safety) will also be monitored. Data will be pseudonymized and analyzed descriptively to estimate variability and preliminary effects, informing the design of a definitive trial. Expected Results: It is hypothesized that Pilates will produce clinically meaningful improvements in balance, pain, sleep quality, and health-related quality of life compared with ergonomics education, with acceptable feasibility and safety outcomes. Conclusions: This randomized controlled trial will provide initial evidence regarding the efficacy and feasibility of Pilates as a complementary rehabilitation strategy for women with osteoporosis and provide key parameters to optimizing a future adequately powered trial. Ethics and Dissemination: This study will be conducted in accordance with the principles of the Declaration of Helsinki and has been approved by the Human Ethics Committee of Universidad Rey Juan Carlos. Potential risks will be minimized, and any adverse events will be systematically recorded and addressed.

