The sample size was estimated using G*Power version 3.1, based on a two-tailed independent samples *t*-test comparing the means between two groups (experimental and control). The following parameters were used: an effect size (Cohen’s d) of 0.58, a significance level (α) of 0.05, a statistical power (1−β) of 0.85, and an allocation ratio (N_2_/N_1_) of 1. Under these assumptions, the required sample size was 110 participants in total (55 per group) to detect a moderate effect size with 85% power and a 5% type I error rate. To account for potential attrition of 15% during the 12-week follow-up, the final recruitment target was increased to approximately 126 participants in total (63 per group).

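### The 15% attrition allowance is miscalculated: 126 randomised women leave about 107 evaluable, not the 110 the plan requires

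*Protocol article*

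**What the plan says.** The sample-size paragraph in section 2.3 (Procedure) of the protocol article gives its inputs in full. The calculation is "based on a two-tailed independent samples" t-test with equal allocation, "an effect size (Cohen’s d) of 0.58", "a significance level (α) of 0.05" and "a statistical power (1−β) of 0.85". From these it concludes that "the required sample size was 110 participants in total (55 per group").

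The attrition step follows. "To account for potential attrition of 15% during the 12-week follow-up", the article says, "the final recruitment target was increased to approximately 126 participants in total (63 per group"). The formula for this step is not written out. The Abstract repeats the target without the qualifier: "A total of 126 (63 per group) postmenopausal women".

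**The concern.** Attrition during follow-up is a loss from the women who were randomised. To finish with a required number after losing a fraction *a*, that number must be divided by (1 − *a*). Multiplying by (1 + *a*) always gives a smaller target, and the figures here look like the product of that multiplication.

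If so, the plan claims a combination of 15% attrition, 110 evaluable women and 85% power that its recruitment target does not deliver. This is the article's only justification of its sample size. A final report that repeated it would claim a power the trial did not have at the attrition it planned for.

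**Working it through.** **Inputs**, all from section 2.3: two-sided two-sample t-test; d = 0.58; α = 0.05; power 0.85; allocation 1:1; 110 required (55 per group); attrition 15%; target 126 (63 per group).

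**1. Reproduce the 110.** Power comes from the noncentral t distribution with n₁ + n₂ − 2 degrees of freedom and noncentrality d × √[n₁n₂ / (n₁ + n₂)]. Solving for 85% gives 54.36 per group.

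- 54 per group: power 84.8%
- 55 per group: power 85.4%

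So 55 is the smallest equal group size that reaches 85%, and 110 reproduces exactly. The base calculation is right.

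**2. Reproduce the 126.**

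- Multiplying: 110 × 1.15 = 126.5, and 55 × 1.15 = 63.25. These match the stated 126 and 63.
- Dividing: 110 / 0.85 = 129.4, and 55 / 0.85 = 64.7, so 65 per group and 130 in total. These do not match.

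**3. Test the target against its own purpose.** This step does not depend on which formula was used.

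- Evaluable after 15% loss: 126 × 0.85 = 107.1, or 63 × 0.85 = 53.55 per group
- Shortfall against 110: about 3 evaluable women
- Largest attrition that still leaves 110: 1 − 110/126 = 12.7%
- Check of the alternative: 130 × 0.85 = 110.5, which does leave 110

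**4. Effect on power and on the detectable difference** (same noncentral t calculation).

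| Evaluable women | Power at d = 0.58 | d detectable with 85% power |
|---|---|---|
| 110 (55 + 55) | 85.4% | 0.577 |
| 107 (53 + 54) | 84.4% | 0.585 |
| 106 (53 + 53) | 84.1% | 0.588 |

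The 107 row is the one that corresponds to 15% loss from 126. The 106 row shows the result if 53.55 is rounded down in both groups.

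**The case against.** The best case on the other side is that nothing of consequence follows.

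- **The gap is very small.** The unrounded requirement is 2 × 54.36 = 108.7, so 107.1 misses the true 85% threshold by fewer than two women. The power lost against 85% is about 0.6 percentage points, well inside the uncertainty of both the 15% and the 0.58. This stands, and it limits how far the point can be pressed.
- **The planned analysis may make up the loss.** Section 2.3 foresees ANCOVA with baseline values as covariates, where appropriate. The article gives no correlation between baseline and follow-up, so one has to be assumed. With 107 evaluable women, power would be about 85.8% at a correlation of 0.2, 87.6% at 0.3 and 92.9% at 0.5. This softens the consequence. It does not repair the statement, because the sample size is based on an unadjusted t-test and claims no such gain.
- **Stopping the intervention need not mean a lost outcome.** Section 2.5.3 plans to collect post-intervention assessments from women who discontinue, when feasible. Actual loss may therefore be below 15%, but the plan's own allowance is still 15%.
- **Multiple imputation is planned.** It can limit bias, but it does not restore the information in outcomes that were never observed.
- **The target is called approximate.** It is nevertheless fixed at 63 per group and repeated without that qualifier in the Abstract. Rounding 129.4 does not give 126.
- **The formula is inferred.** This is true, and multiplication by 1.15 should be described as the apparent route. The finding itself needs only 126 × 0.85.

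**Conclusion.** The point holds. The required number of 110 is correct, but the attrition step is not: 126 randomised women do not leave 110 after a 15% loss. They leave about 107, four fewer are randomised than the 130 that would be needed, and power is 84.4% where 85% was planned. The target supports attrition of at most 12.7%.

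The power figures rest on the article's own assumptions (d = 0.58, two-sided α of 0.05, unadjusted t-test) and on losses split almost equally between the groups. This is a clear arithmetic error with a minor effect. It should be corrected because the sample size rests on it, but it gives no ground for calling the trial materially underpowered.

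**What to change.** Keep 126 and correct the sentence in section 2.3. Either of these wordings would do:

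- A target of 126 (63 per group) allows for about 12.5% attrition (126 × 0.875 = 110.25).
- With 15% attrition, 126 randomised women leave about 107 evaluable, giving about 84% power at d = 0.58.

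This costs one sentence and no extra participants. The stated attrition allowance or power becomes slightly less favourable, and the Abstract needs no change.

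If the sponsor prefers to keep both 15% attrition and 85% power, the target should read 130 (65 per group), in section 2.3 and in the Abstract. That costs four more women. Given the size of the shortfall, it is optional.

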### 2.4. Intervention

This study will employ a RCT design with parallel groups and a single-blind approach (evaluator blinding).

Participant allocation will be performed using computer-generated randomization. The randomization sequence will be created with the OxMaR software, a tool specifically designed for minimization and randomization in clinical trials [20]. This software will enable the random assignment of participants into two groups: a control group (CG), which will receive education on postural ergonomics techniques applied to activities of daily living, and an experimental group (EG), which will participate in Pilates Method sessions.

Each participant’s allocation number will be sealed in an opaque envelope and delivered to the researchers responsible for implementing the interventions in both the CG and EG. The evaluator conducting the outcome assessments will remain blinded to group allocation and will not have access to any information regarding participants’ assigned groups.

Following randomization and baseline assessment, the 12-week intervention period will begin. Upon completion, the same assessment battery will be re-administered to evaluate post-intervention outcomes and determine whether statistically significant differences exist between groups.

The CG will participate in two educational sessions on ergonomics and postural hygiene, each lasting 60 min and held six weeks apart. These sessions will aim to improve functional performance during activities of daily living by promoting safe movement strategies, spinal alignment, proper body mechanics, and fall prevention. This approach was designed in accordance with current clinical practice guidelines and expert recommendations on ergonomics and postural hygiene in osteoporosis management [21,22,23]. Each session will be jointly conducted by a physiotherapist and an occupational therapist with experience in osteoporosis management. Participants will receive illustrated brochures and short video demonstrations developed by the research team, based on established postural hygiene guidelines, to reinforce learning.

The EG will undergo Pilates Method training consisting of one-hour sessions held twice weekly for 12 consecutive weeks. All Pilates exercises will be performed on a mat and will emphasize the core activation principles characteristic of the method. Sessions will be supervised by a physiotherapist and an occupational therapist certified in the Pilates Method, both with over ten years of professional experience in the management of individuals with osteoporosis and musculoskeletal conditions. The specific intervention protocol for the EG is detailed in Table 1.

An individualized baseline assessment will be performed to adapt the exercises to each participant’s physical condition and functional limitations, ensuring that all contraindicated movements are avoided. The training intensity will be monitored using the Borg CR-10 [24] perceived exertion scale, maintaining a moderate intensity level between 4 and 6 points, corresponding to approximately 50–70% of the maximum heart rate (%HRmax). Participants will wear smart bands (Xiaomi Smart Band 9 Active) during all sessions to continuously record heart rate and oxygen saturation, ensuring objective consistency in workload monitoring. Each participant will be informed of their individual %HRmax prior to starting the sessions to facilitate self-awareness and control of exercise intensity. Each session will include approximately 20 min of warm-up, 30 min of core Pilates exercises, and 10 min of cool-down, with short rest intervals of 30–60 s between exercises included within the total session duration. The number of repetitions and weekly progression of the exercises are detailed in Table 1. Continuous supervision will be provided throughout all sessions to guarantee a safe and controlled training environment. In the event of any discomfort or adverse incident, the activity will be immediately discontinued. The participant timeline is illustrated in Figure 1.

### 2.5. Measures

An initial assessment will be conducted during which the evaluation tests described below will be administered. A second assessment will take place following the intervention period (after two months).

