## 2. Materials and Methods

### 2.1. Study Design

A single-blind, RCT with a three-month intervention period will be conducted at Physiocare Madrid, located in the Autonomous Community of Madrid, Spain.

The development of this study protocol followed the SPIRIT 2025 guidelines [18]. This study will be prospectively registered at ClinicalTrials.gov and conducted in accordance with the CONSORT 2010 guidelines to ensure transparent and accurate reporting of its methodology and outcomes [19].

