Although this protocol does not specifically target bone mineral density (BMD), previous studies have demonstrated improvements in several of the variables analyzed in the present research. Cronin et al. [15] and McLaughlin et al. [17] reported no significant changes in lumbar spine or hip BMD but did observe improvements in functional capacity and physical well-being. Similarly, Fernández-Rodríguez et al. [11] found that, even in the absence of BMD changes, participants achieved clinically meaningful improvements in function and quality of life. Therefore, this study prioritizes functional, pain-related, and quality-of-life outcomes, aligning with the current research trend emphasizing functional recovery over bone density alone.

Beyond osteoporosis, a growing body of evidence supports the efficacy of the Pilates Method across various chronic conditions. García-Bravo et al. [41] observed significant improvements in balance, coordination, gross and fine motor dexterity, self-perception, and independence in activities of daily living among individuals’ post-stroke. Çoban et al. [42] reported improvements in dynamic balance in patients with Parkinson’s disease following Pilates training. Likewise, in individuals with multiple sclerosis, Pilates has been associated with enhanced gait, balance, fatigue, strength, stability, and health-related quality of life [43,44].

A potential limitation of this study is the imbalance in the amount of contact time between the intervention and control groups. While the experimental group will participate in 24 supervised Pilates sessions, the control group will only attend two educational sessions on ergonomics and daily living activities. This difference in exposure and interaction with healthcare professionals may introduce an attention or expectation bias, potentially influencing participants’ perception of improvement or adherence. However, this design choice was made to ensure that the control group receives a minimal but ethically appropriate level of health education, without introducing confounding physical activity components. The potential impact of this imbalance will be acknowledged and carefully considered when interpreting the study results.

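### Section 2.5 dates the only outcome visit at two months, which cannot be squared with a 12-week programme assessed on completion

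*Protocol article*

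**What the plan says.** Section 2.5 (Measures) describes an initial assessment and then states: "A second assessment will take place following the intervention period (after two months"). No other place in the article mentions two months.

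The other timing statements agree with one another:

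- Section 2.1: "RCT with a three-month intervention period will be conducted".
- Section 2.4: "Following randomization and baseline assessment, the 12-week intervention period will begin", and then "Upon completion, the same assessment battery will be re-administered to evaluate post-intervention outcomes".
- Section 2.4, Pilates arm: "one-hour sessions held twice weekly for 12 consecutive weeks".
- Section 2.3, sample size: "To account for potential attrition of 15% during the 12-week follow-up".
- Section 4: "the experimental group will participate in 24 supervised Pilates sessions".
- Table 1: the last exercise block runs to week 12.
- Abstract: a 12-week trial with evaluations at baseline and after the intervention only.

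No later follow-up visit is described anywhere.

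**The concern.** The trial has a single post-baseline assessment, so its date is the time point of every outcome: TUG, Functional Reach, FIM, VAS, PSQI, WHOQOL-BREF, QUALEFFO-41 and CSQ-8. Section 2.5 is the natural place for an assessor to look when booking that visit, and the elapsed time it gives does not match the schedule in the rest of the article.

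A visit at two months from the start would compare the arms while the Pilates programme was still running. A visit two months after the end would measure how well the benefit lasts, beyond the 12-week period to which the attrition allowance refers. If the phrase were applied differently from one participant to the next, the outcome time would vary within the trial.

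The PSQI is affected as well, because it asks about the previous month. Its recall window would cover roughly weeks 4 to 8 or weeks 16 to 20, instead of weeks 8 to 12.

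**Working it through.** **Inputs.** Programme length is 12 weeks (Sections 2.3 and 2.4, Abstract) or three months (Section 2.1). Sessions are two per week, 24 in total (Sections 2.4 and 4). The bracketed visit time is two months (Section 2.5). Section 2.3 gives d = 0.58, two-sided alpha 0.05, power 0.85 and 55 per group.

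**Step 1: can two months be a rounding of 12 weeks?** One month = 365.25/12 = 30.44 days.

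- 12 weeks = 84 days; 84/30.44 = 2.76 months. This rounds to three, in line with Section 2.1, and not to two.
- Two months = 60.9 days; 60.9/7 = 8.7 weeks (8 weeks if a month is counted as four weeks).

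**Step 2: where does each reading put the visit?**

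| Reading | Visit week | Pilates sessions delivered |
|---|---|---|
| On completion (Section 2.4) | 12 | 24 of 24 |
| Two months from the start | 8 to 8.7 | 2 × 8 = 16 to 2 × 8.7 = 17.4, so about 16 to 17 of 24 |
| Two months after the end | 12 + 8 = 20 to 12 + 8.7 = 20.7 | 24 of 24, then two months without sessions |

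The second row falls 12 − 8.7 = 3.3 to 12 − 8 = 4 weeks before the programme ends. The third contradicts both re-assessment on completion and a 12-week follow-up. Neither gives week 12.

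**Step 3: the plan's own sample size.** For a two-sided t-test with n per group, the noncentrality is d × √(n/2) on 2n − 2 degrees of freedom. With d = 0.58 and n = 55 it is 0.58 × √27.5 = 3.04 on 108 degrees of freedom, and power is 0.854. With n = 54, power is 0.848. So 55 per group (110 in total) reproduces. It does not depend on the visit date and does not change with the fix.

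**Step 4: a hypothetical loss of power on the early reading only.** Two assumptions are added that the article does not state: 0.58 is the effect at the end of the programme, and benefit grows in proportion to sessions attended.

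- 16 sessions: d = 0.58 × 16/24 = 0.387; noncentrality 0.387 × √27.5 = 2.03; power 0.52.
- 17 sessions: d = 0.58 × 17/24 = 0.411; noncentrality 0.411 × √27.5 = 2.15; power 0.57.
- If all benefit is reached by week 8: d stays 0.58 and power stays 0.854.

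The range on this reading is therefore from no loss to a fall from 85% to about 52%.

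**The case against.** The strongest reply is that the article already dates the visit correctly. Section 2.4 ties it to completion of the 12 weeks, the Abstract and the sample size text agree, and the main clause of the Section 2.5 sentence itself places the visit after the intervention period. One discordant bracket, probably left over from an earlier text, would then leave the visit at week 12 with nothing lost. This largely stands. It makes the intention fairly clear, but it does not make the text consistent: the bracket remains a stated time that fits no part of the schedule.

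A reader might infer that the trial will measure outcomes before the programme ends and so has only 52% to 57% power. The documents do not support that. The early reading goes against the sentence's own main clause, no statement says that benefit is proportional to sessions, and Section 2.3 ties 0.58 to no outcome or time point. A reader might also infer that nothing but Section 2.5 dates the visit. That is not so, because Section 2.4 dates it by event.

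Figure 1 (participant timeline) was not available for this check and may state the visit week. It could show what staff would follow, but it would not remove the conflict between the two sections. The absence of a visit window is not an error either, since a journal article commonly leaves that to the full protocol.

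**Conclusion.** The point holds as an internal contradiction about when the only outcome assessment takes place. Two months is 3.3 to 4 weeks too early if counted from the start, and 8 to 8.7 weeks too late if counted from the end. This follows from calendar arithmetic and needs no assumption.

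The most likely explanation is a drafting slip, with assessment on completion as the intention. The correction still deserves to be made before visits are scheduled, because the phrase governs every outcome and there is no second visit to fall back on. The power figures are an illustration for one reading under a stated assumption. They are not an estimate of what the trial will lose.

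**What to change.** In Section 2.5, replace the bracketed two-month phrase with wording that places the second assessment on completion of the 12-week intervention. State that the same time point applies in both arms. This matters because the control arm has only two sessions, six weeks apart, and so its last session does not mark the end of the 12 weeks. Check that Section 2.4, Section 2.5 and the timeline figure then say the same thing.

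If a visit at two months, or a follow-up two months after the end, was in fact intended, Sections 2.3 and 2.4 and the Abstract would have to be rewritten to match.

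The cost is one phrase. The correction adds no participants, visits or procedures, and the sample size calculation is unchanged.
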